## Abstract

**Background:**

Surgical site infections remain a frequent and clinically relevant complication following elective open vascular groin surgery, particularly in procedures involving implantation of alloplastic material. Despite routine use in many surgical disciplines, the role of standardized intraoperative wound irrigation in vascular groin surgery is insufficiently defined. Hypochlorous acid is a physiologically occurring antimicrobial agent with broad-spectrum activity and favourable tissue compatibility, making it a promising option for intraoperative wound lavage. However, clinical evidence for its preventive use in elective vascular groin procedures is limited.

**Methods:**

Hypoclates:vascular is a single-centre, ambispective cohort study conducted at Heidelberg University Hospital. Adult patients undergoing elective open vascular groin surgery with arterial exposure are included. A departmental standard change introduced intraoperative wound irrigation with at least 250 ml hypochlorous acid–containing Granudacyn^®^ prior to wound closure, with additional irrigation of alloplastic material where applicable. Patients treated before this change form a retrospective control cohort without antiseptic lavage, while those treated thereafter constitute the prospective cohort. The primary outcome is the incidence of surgical site infections classified according to Centers for Disease Control and Prevention criteria. Secondary outcomes include postoperative morbidity, wound-related complications, antibiotic use, length of hospital stay, and overall morbidity assessed by the Comprehensive Complication Index. Multivariable logistic regression will be used to explore associations between hypochlorous acid-based irrigation and infectious outcomes.

**Discussion:**

This study provides a pragmatic real-world evaluation of standardized hypochlorous acid-based intraoperative wound irrigation in elective open vascular groin surgery. The results will clarify whether this physiologically compatible antiseptic approach is associated with reduced surgical site infections and postoperative morbidity, thereby informing the design of future randomized trials and evidence-based perioperative standards in vascular surgery.

**Trial registration:**

The study was registered on 25 March 2026 in the German Clinical Trials Register (registration identifier: DRKS00039521) prior to data acquisition.

## Background

In vascular surgery, surgical site infections (SSI) represent a severe complication, particularly following procedures involving surgical exposure of the groin [1–4]. The anatomical characteristics of the groin region, including dense lymphatic structures and proximity to bacterial colonisation sites, contribute to an increased susceptibility to postoperative wound complications. In the presence of vascular prostheses or patches, infections are further associated with high revision rates and substantial procedure-related mortality due to foreign material involvement [5–8]. Reported SSI rates following elective open groin vascular procedures vary substantially depending on patient characteristics, urgency of surgery, and degree of tissue ischemia. Contemporary studies report SSI incidences ranging from approximately 5–10% in lower-risk elective procedures to more than 25–30% in higher-risk groin reconstructions involving prosthetic material or advanced peripheral arterial disease [9–11].

While intraoperative wound lavage is commonly performed in many surgical disciplines, inconsistent evidence and guideline recommendations suggest heterogeneous use and lack of uniform standardisation across clinical practice, including vascular surgery and elective groin procedures [12]. Accordingly, available evidence regarding the effectiveness of intraoperative lavage in reducing SSI is limited and inconsistent, and there are no definitive procedure-specific data for elective groin procedures in vascular surgery [13, 14].

The use of antiseptic solutions for intraoperative lavage has been proposed as a strategy to enhance microbial control, yet concerns regarding tissue toxicity and impaired wound healing have restricted their routine use [15, 16]. In this context, hypochlorous acid (HOCl) is of particular interest, as it represents a physiologically occurring antimicrobial molecule generated by the innate immune system and is characterised by broad-spectrum microbicidal activity combined with high tissue compatibility [17, 18].

To date, clinical data on HOCl-based lavage in vascular surgery are scarce. Large-scale observational studies and randomised trials specifically addressing elective groin vascular procedures are lacking [19]. Experimental data demonstrate favourable cytocompatibility [17, 20], supported by animal models and clinical studies in other surgical and wound care settings [21–24]. Importantly, HOCl decomposes into non-toxic by-products, distinguishing it from other antiseptics such as polyhexanide, chlorhexidine (CHX), or octenidine [15].

Although established antiseptics such as CHX and povidone-iodine remain widely used in surgical antisepsis, their intraoperative application as lavage solutions may be limited by concerns regarding local tissue toxicity, fibroblast impairment and delayed wound healing, particularly in vulnerable or ischemic tissue environments [25, 26].

In contrast, the rationale for HOCl-based lavage is not necessarily superior antimicrobial potency in every setting, but rather its potentially favourable balance between antimicrobial activity and tissue compatibility. Experimental and translational studies suggest that HOCl may provide effective microbial control with comparatively low cytotoxicity, favourable wound-healing characteristics and reduced local irritation [25–28].

In addition, HOCl-based irrigation may potentially offer advantages in disrupting microbial biofilms on implanted foreign material such as vascular grafts, patches or clips, which may be particularly relevant in vascular surgery where prosthetic-material associated infections are associated with high morbidity and complex revision procedures [29–33].

Granudacyn^®^, a CE-marked medical device containing HOCl as its active component, is already established in clinical wound management and approved for use in cleansing, irrigation and moistening of acute, chronic, contaminated and surgical wounds, including application in body cavities such as the peritoneal cavity [24, 34]. However, evidence for its preventive application as part of routine intraoperative wound management in elective groin vascular surgery remains limited [12].

The microbial burden required to initiate an SSI is lower than that associated with established wound infection [35]. In elective groin vascular surgery – where prosthetic material is frequently implanted – even modest reductions in bacterial contamination may be clinically relevant. Given its favourable tissue compatibility, HOCl may provide a low-risk option for intraoperative wound lavage as part of routine surgical practice, potentially reducing SSI risk without the adverse effects associated with more aggressive antiseptic agents [18].

## Methods

### Study design

HYPOCLATES:VASCULAR is a single-centre, ambispective, controlled observational cohort study with a retrospective control group conducted at the Department of Vascular and Endovascular Surgery at Heidelberg University Hospital. The study evaluates the clinical impact of a departmental standard change in intraoperative wound management during elective open vascular groin procedures with arterial exposure. Reporting follows the STROBE statement for observational studies [36], and the study protocol was developed in accordance with the SPIRIT guidelines [36, 37].

Patients treated prior to the implementation of the new standard, in whom no antiseptic wound lavage was performed, constitute the retrospective control cohort. The prospective cohort comprises patients undergoing surgery after the standard change who receive intraoperative wound irrigation with a minimum volume of 250 ml of Granudacyn^®^ prior to wound closure. Granudacyn^®^ is a pH-neutral hypotonic electrolyte solution containing stabilised HOCl (50 ppm) and sodium hypochlorite (50 ppm) in equilibrium [38]. In cases requiring implantation of alloplastic material, the graft is additionally irrigated with Granudacyn^®^ before implantation.

The introduction of this standard occurs independently of the study and is not influenced by study participation. No additional diagnostic or therapeutic interventions are required beyond routine perioperative care, including established protocols for antibiotic prophylaxis. Data collection is limited to routinely documented clinical parameters.

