### Study flow

All patients undergoing elective open vascular groin surgery during the study period will be screened for eligibility and may be excluded according to predefined criteria. Patients treated prior to the implementation of the new intraoperative wound management standard, in whom no antiseptic wound lavage was performed, will constitute the retrospective control cohort.

Following the departmental standard change on 1 March 2026, all eligible patients will receive an intraoperative wound irrigation of the groin with HOCl–containing Granudacyn^®^ (≥ 250 ml) prior to wound closure. In cases involving implantation of alloplastic material, the graft will additionally be irrigated with Granudacyn^®^ before implantation. Patients treated after the standard change will form the prospective cohort. The retrospective and prospective observation periods each comprise six months, with the overall study period spanning from 1 September 2025 to 31 August 2026. Post-discharge follow-up is routinely scheduled six weeks after surgery as part of standard vascular surgical aftercare and typically includes clinical wound assessment and routine laboratory testing. Outcomes documented during this routine follow-up, including delayed SSI occurring after hospital discharge, will additionally be captured descriptively where available. A schematic overview of patient inclusion and cohort allocation is shown in Fig. 1.

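### The prospective cohort is defined by lavage received in one section and by date of surgery in others, so post-change patients with no or incomplete lavage have no fixed place

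*Protocol article*

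**What the plan says.** The prospective cohort is described in three places.

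- Study design: "The prospective cohort comprises patients undergoing surgery after the standard change who receive intraoperative wound irrigation with a minimum volume of" 250 ml. Membership needs both a date and a treatment received.
- Study flow: "Patients treated after the standard change will form the prospective cohort". Membership needs a date only.
- Abstract, Methods: "those treated thereafter constitute the prospective cohort". Again a date only.

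Study flow also states that after the change "all eligible patients will receive an intraoperative wound irrigation of the groin", which would make the wordings equivalent if it held without exception.

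The control cohort is described consistently. Study design has "Patients treated prior to the implementation of the new standard, in whom no antiseptic wound lavage was performed, constitute the retrospective control cohort", Study flow uses the same clause on lavage, and the abstract has "Patients treated before this change form a retrospective control cohort without antiseptic lavage".

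Table 1 sets eligibility at scheduling and has no condition on lavage. The aim in Study design is a contrast between standards: "The study evaluates the clinical impact of a departmental standard change in intraoperative wound management". The primary analysis in the Statistical analysis section is worded as the association between HOCl irrigation and surgical site infection (SSI).

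**The concern.** A patient operated on after 1 March 2026 who gets no lavage, or less than the minimum volume, is in the prospective cohort under Study flow and the abstract. Under Study design the same patient is in neither cohort. No section resolves this, so the exposure term in the primary regression can be coded in two ways and the analysed population can differ.

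The receipt wording also selects after eligibility, and in one arm only. If lavage is omitted or cut short in operations that carry a different SSI risk, those cases leave the post-change cohort while comparable pre-change cases stay among the controls. The contrast is then no longer between all eligible cases under the old standard and all eligible cases under the new one. The stated purpose is to estimate effect sizes for later randomised trials, and the planning rates imply only about 14 and 7 events, so a few patients moved in or out can shift the estimate.

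**Working it through.** **Inputs from the Sample size section.** 80 cases per cohort, SSI rates of 17.5% (control) and 8.75% (HOCl), two-sided Fisher's exact test at 0.05, stated power 29.9%.

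**The plan's own figure.** Summing the binomial probabilities of all 80 × 80 tables with Fisher p ≤ 0.05 gives a power of 29.89%, so the stated 29.9% reproduces and is not in question. Expected events are 80 × 0.175 = 14 and 80 × 0.0875 = 7. The planned odds ratio (OR) is (0.0875/0.9125) / (0.175/0.825) = 0.452.

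**Assumed inputs.** The documents give no uptake figure and no risk for patients who miss the lavage. Let f be the share of post-change cases without the full lavage, and RR their SSI risk relative to those who received it.

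**Check 1: selection with no true effect.** Set the overall SSI risk at 17.5% in both periods. The risk r among those who received the lavage solves (1 − f)r + f·RR·r = 0.175, so

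r = 0.175 / (1 − f + f·RR), and OR = [r/(1 − r)] / (0.175/0.825).

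For f = 10% and RR = 2: r = 0.175/1.1 = 0.1591 and OR = 0.1892/0.2121 = 0.892. For f = 10% and RR = 3: r = 0.175/1.2 = 0.1458 and OR = 0.1707/0.2121 = 0.805 (0.80 to two decimals).

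| f | RR = 1 | RR = 2 | RR = 3 |
|---|---|---|---|
| 5% | 1.000 | 0.943 | 0.892 |
| 10% | 1.000 | 0.892 | 0.805 |
| 20% | 1.000 | 0.805 | 0.673 |

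The correct answer in every cell is 1.000. The receipt-based cohort is unbiased in the first column and otherwise favours the lavage. If those who missed it were at lower risk, the bias would run the other way.

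**Check 2: what the date definition costs.** Suppose the lavage works as planned, and that patients who miss it have the control risk of 17.5%. The post-change rate is then (1 − f) × 0.0875 + f × 0.175.

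| f | Post-change rate | Date-based OR | Fisher power, 80 vs 80 |
|---|---|---|---|
| 5% | 9.19% | 0.477 | 26.7% |
| 10% | 9.63% | 0.502 | 23.7% |
| 20% | 10.50% | 0.553 | 18.5% |

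The receipt-based OR stays at 0.452 here, because non-receipt is unrelated to underlying risk. These shifts are dilution, not bias: they are the effect of the standard as actually delivered.

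**The case against.** The best defence is that Study design merely describes the new standard. Study flow expects all eligible patients to receive the lavage, exclusions are said to follow predefined criteria, and Table 1 has none on lavage. On this reading nobody is dropped. This stands in part: the loss of patients follows from the cohort sentence and is not a written exclusion rule. But the standard is introduced independently of the study, which does not control delivery, and the text leaves the incomplete case open.

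The regression also adjusts for contamination class, procedure type, alloplastic material and duration of surgery, which may absorb part of the reason for omission. Residual bias is acknowledged under Study limitations, and all analyses are exploratory. These points limit the harm but do not settle who is analysed.

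Four stronger readings are tempting, and the documents do not support them.

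- A reader might infer that controls too are selected on treatment received. The clause "in whom no antiseptic wound lavage was performed, constitute the retrospective control cohort" is worded alike in Study design and Study flow. It reads naturally as a description of earlier practice, as in the abstract and in the primary hypothesis. No section says that any pre-change patient had an antiseptic lavage.
- A reader might infer that cohort membership cannot be verified, because lavage and volume are not named under Data collection. The date of surgery is listed there, so the date definition can be checked. Lavage may also fall under the general item on institutional prevention measures, and an article need not itemise the extraction sheet.
- A reader might infer that the protocol's question can only be answered by date. The aim in Study design points that way, but Study population, the primary hypothesis and the primary analysis refer to irrigation itself. The date definition is the better supported choice, not one that the text dictates.
- A reader might take shifts in the OR under assumed non-receipt as the size of the bias. Some such shifts are dilution, as Check 2 shows.

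**Conclusion.** The contradiction about the prospective cohort stands in the current text and should be resolved before analysis. It has an effect only if uptake falls short of 100%, and it biases the comparison only if non-receipt is also related to SSI risk. Under assumed non-receipt of 10% at two to three times the risk, a true OR of 1.00 would appear as about 0.89 to 0.80. With 5% at double the risk it would be 0.94, with 20% at triple the risk 0.67, and with no relation to risk 1.00. The actual size cannot be derived from the documents. The stated power is unaffected as arithmetic. For the control cohort, only a safeguard in wording is warranted.

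**What to change.** - Reconcile Study design with Study flow and the abstract: for the primary comparison, define both cohorts by date of surgery (before, or on or after, 1 March 2026) among all eligible cases.
- Reword the control clause so that it describes earlier practice and cannot act as an exclusion.
- Name lavage given, fluid and volume explicitly among the extracted variables for both cohorts, where documented.
- Report adherence in the post-change cohort.
- Use lavage received only in a sensitivity analysis.

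This costs a sentence in each of the two sections and a few extraction fields. Data acquisition is still under way, so it can be done before outcomes are analysed. The price is dilution of the irrigation effect if uptake is incomplete: on the planning rates and 10% non-receipt at the control risk, the expected OR moves from 0.45 to 0.50. The sensitivity analysis would show the receipt-based estimate beside it.

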### Study population

The study population comprises adult patients (aged ≥ 18 years) undergoing elective open vascular groin surgery with arterial exposure. This cohort represents a clinically relevant population with an increased risk of SSI, particularly in the setting of vascular reconstruction and potential implantation of alloplastic material.

By focusing on a homogeneous group of elective procedures performed in a standardized anatomical region, the study aims to evaluate the effect of HOCl–based intraoperative wound irrigation under real-world clinical conditions while minimizing procedure-related heterogeneity that could confound postoperative infectious outcomes.

Patients unable to receive standard perioperative antibiotic prophylaxis as well as pregnant or breastfeeding individuals were excluded, with pregnancy defined as the period from conception until the end of gestation. Eligibility criteria are summarized in Table 1.

**Table 1 Tab1:** Inclusion and exclusion criteria

Inclusion criteria	Exclusion criteria
Adults (≥ 18 years old) scheduled for elective open vascular groin surgery with arterial exposure	Contraindication to or inability to receive standard perioperative antibiotic prophylaxis
	Pregnant or breastfeeding women

### Study flow

All patients undergoing elective open vascular groin surgery during the study period will be screened for eligibility and may be excluded according to predefined criteria. Patients treated prior to the implementation of the new intraoperative wound management standard, in whom no antiseptic wound lavage was performed, will constitute the retrospective control cohort.

Following the departmental standard change on 1 March 2026, all eligible patients will receive an intraoperative wound irrigation of the groin with HOCl–containing Granudacyn^®^ (≥ 250 ml) prior to wound closure. In cases involving implantation of alloplastic material, the graft will additionally be irrigated with Granudacyn^®^ before implantation. Patients treated after the standard change will form the prospective cohort. The retrospective and prospective observation periods each comprise six months, with the overall study period spanning from 1 September 2025 to 31 August 2026. Post-discharge follow-up is routinely scheduled six weeks after surgery as part of standard vascular surgical aftercare and typically includes clinical wound assessment and routine laboratory testing. Outcomes documented during this routine follow-up, including delayed SSI occurring after hospital discharge, will additionally be captured descriptively where available. A schematic overview of patient inclusion and cohort allocation is shown in Fig. 1.

**Fig. 1 Fig1:**
[figure not shown]
Study flow of HYPOCLATES:VASCULAR

Study participation requires no additional procedures, diagnostics, or interventions beyond routine clinical care and imposes no additional burden on patients or clinical staff. Consequently, no separate patient information or informed consent is required for the prospective cohort. If the predefined sample size is not reached within the planned observation period, the respective cohort period may be extended.

Apart from the implementation of HOCl-based wound irrigation, perioperative management and SSI prevention standards including antibiotic prophylaxis, skin antisepsis, surgical workflows, and postoperative care remain unchanged throughout both study periods.

### Data collection

Data collection focuses on clinically relevant variables routinely documented as part of perioperative vascular surgical care and considered relevant for postoperative infectious outcomes and risk adjustment. All data will be extracted from the patients’ electronic medical records using the hospital’s digital documentation system (SAP i.s.h.med).

Demographic and baseline clinical variables will include sex, age, body mass index, The American Society of Anaesthesiologists (ASA) physical status classification, smoking status, alcohol misuse, and relevant comorbidities. These comprise diabetes mellitus (requiring treatment with metformin or insulin analogues), chronic kidney disease (requiring dialysis or fluid restriction), chronic obstructive pulmonary disease, immunologic disorders, ongoing immunosuppressive therapy, known bacterial colonization (MRSA, VRE, 3-/4-MRGN), history of previous vascular or groin surgery, and the Charlson Comorbidity Index (Charlson-Index).

Preoperative laboratory parameters will include haemoglobin, white blood cell count, C-reactive protein, serum albumin, and renal function parameters as routinely documented.

Procedure-related variables will include date and type of elective vascular groin surgery with arterial exposure (e.g. endarterectomy, bypass surgery, patch angioplasty, or prosthetic graft implantation), surgical approach, and total duration of the procedure. Severity of peripheral arterial disease and indication for surgery (including Rutherford classification where applicable) will be recorded. Intraoperative data will further include the antiseptic agent used for skin preparation, the degree of wound contamination according to the Centers for Disease Control and Prevention (CDC) classification (clean, clean-contaminated, contaminated, or dirty/infected), perioperative blood loss and transfusion requirements, primary wound closure, placement and type of surgical drains, and implantation of alloplastic material.

Additional intraoperative variables potentially associated with SSI risk will be recorded where routinely documented. These include perioperative glucose management in diabetic patients, perioperative temperature management, use of antimicrobial-coated sutures, preoperative hair removal practice, and other relevant institutional SSI prevention measures.

Details on perioperative antibiotic prophylaxis will be recorded, including the administered agent, timing, redosing, and duration in accordance with institutional standards.

Infection-related outcomes will focus on the occurrence and classification of SSI according to CDC criteria [39], based on clinical and microbiological findings documented during index hospital stay. SSI will be categorized as follows:

Superficial incisional SSI: Infection involving only the skin or subcutaneous tissue of the incision, meeting at least one of the CDC-defined criteria.Deep incisional SSI: Infection involving the deep soft tissues (e.g. fascia or muscle layers) of the surgical site, fulfilling CDC criteria.Organ/space SSI: Infection involving any anatomical structure other than the incision that was opened or manipulated during the surgical procedure, fulfilling CDC criteria.

Postoperative complications will include lymphatic fistula, haematoma, seroma, wound dehiscence, postoperative bleeding, graft-related complications, thrombotic or embolic events, myocardial infarction, stroke, pneumonia, pulmonary embolism, urinary tract infection, and need for surgical or radiological reintervention. All complications will be graded according to the Clavien–Dindo classification, and the Comprehensive Complications Index (CCI) will be calculated for each patient.

Postoperative management parameters will include length of intensive care unit stay, need for reoperation or radiological intervention, duration of antibiotic therapy, and total length of hospital stay. Postoperative laboratory monitoring will include routine infection markers as documented during the inpatient period. Follow-up data will be collected for up to six weeks postoperatively as part of routine vascular surgical aftercare.

